### **Schedule of Events for outpatients**

| Investigation                                | Screening
(d-4 to
d1) | Day
1                                             | Day
2 | Day
3 | Day
4 | Day
5 | Day 6 | Day 7 | Day 8 | Day 9 | Day 10 | Day 15                                      | Follow-up(day
29)  | Follow-up(day
60)  |
|----------------------------------------------|-----------------------------|------------------------------------------------------|----------|----------|----------|----------|-------|-------|-------|-------|--------|---------------------------------------------|-----------------------------------|-----------------------------------|
| Written
informed
consent               | X                           |                                                      |          |          |          |          |       |       |       |       |        |                                             |                                   |                                   |
| Demographic
and Medical
History        | X                           |                                                      |          |          |          |          |       |       |       |       |        |                                             |                                   |                                   |
| Randomisatio
n                            | X                           |                                                      |          |          |          |          |       |       |       |       |        |                                             |                                   |                                   |
| Observations                     | X                           |                                                      |          |          |          |          |       |       |       |       |        | X                                           | X                                 | X                                 |
| Height and
weight                         | X                           |                                                      |          |          |          |          |       |       |       |       |        | X                                           | X                                 | X                                 |
| Physical Exam                                | X                           |                                                      |          |          |          |          |       |       |       |       |        | Symptom directed where clinically indicated |                                   |                                   |
| AE Evaluation                                | X                           | Continually review from time of consent  |          |          |          |          |       |       |       |       |        |                                             |                                   |                                   |
| Concomitant
Medications                   | X                           | Continually review from time of consent  |          |          |          |          |       |       |       |       |        |                                             |                                   |                                   |
| IMP
Dispensing               |                             | X                                                    |          |          |          |          |       |       |       |       |        |                                             |                                   |                                   |
| IMP
Administration
2                   |                             | X                                                    | X        | X        | X        | X        | X     | X     | X     | X     | X      |                                             |                                   |                                   |
| WHO
performance
status
(Appendix 2) | X                           |                                                      |          |          |          |          |       |       |       |       |        |                                             |                                   |                                   |

| Investigation                                                                   | Screening
(d-4 to
d1) | Day
1        | Day
2 | Day
3 | Day
4 | Day
5 | Day 6 | Day 7 | Day 8          | Day 9 | Day 10 | Day 15 | Follow-up(day
29)  | Follow-up(day
60)  |
|---------------------------------------------------------------------------------|-----------------------------|-----------------|----------|----------|----------|----------|-------|-------|----------------|-------|--------|--------|-----------------------------------|-----------------------------------|
| WHO COVID
Ordinal Severity
Scale
(Appendix 1)              | X                           | X               | X        | X        | X        | X        | X     | X     | X              | X     | X      | X      | X                                 | X                                 |
| Routine Clinical
Blood tests 
(see table 2)                   | X                           |                 |          |          |          |          |       |       |                |       |        | X      | X                                 | X                                 |
| Blood Sample
for PK analysis 
(favipiravir arm
only)      | X              | X  |          |          |          |          |       |       |                |       |        |        |                                   |                                   |
| Blood Samples
for Epigenetic
and
Immunological
testing  | X                           |                 |          |          |          |          |       |       |                |       |        | X      | X                                 | X                                 |
| Viral PCR
(nasopharyngeal
swab)                               | X               |                 |          |          |          |          |       |       | X  |       |        | X      | X                                 | X                                 |
| Viral Load
(nasopharyngeal
swab)                              | X                           |                 |          |          |          |          |       |       | X  |       |        | X      | X                                 | X                                 |
| Pregnancy
Test                                                   | X                           |                 |          |          |          |          |       |       |                |       |        |        |                                   |                                   |
| COVID19 Health
and Wellbeing
Follow up
Survey
(Appendix 3)          |                             |                 |          |          |          |          |       |       |                |       |        | X      | X                                 | X                                 |

1. Observations: Heart rate, temperature, oxygen saturations, blood pressure, respiratory rate
2. IMP should start to be administered within 24 hours of randomisation

3. Bloods/Nasopharyngeal swabs can be taken +/- 48 hours from scheduled time point unless otherwise specified. Screening bloods should be performed within 96 hours of randomisation
4. Nasopharyngeal swabs on day 1 should be taken as close to T0 (time of first drug administration) as possible
5. Follow-up visit at day 15, 29 and may be performed by telephone if patient is unable to attend clinic
6. Serum pregnancy test, for patients of childbearing potential only. Result must be confirmed negative before IMP is released to patient.
7. Screening COVID-19 test can be done using any valid method of testing
8. AE, con med and WHO COVID Ordinal Severity Scale assessments should be made by phone call on days 1 – 10.
9. Optional nasopharyngeal swab may be done by patient at home if possible and safe to transport
10. To minimise the time spent in the clinic, patients can return home after screening and have IMP delivered to their home following randomisation
11. PK sampling should only be done where site have provision to take a predose sample (screening or day 1 pre-dose) AND a post dose sample (30 minutes after dosing), and have facilities to spin samples within 4 hours.

## 1 INTRODUCTION & BACKGROUND

### Description of the proposed trial, patient population and disease area

The proposed trial will assess the efficacy of favipiravir as an early treatment for COVID-19. COVID-19 is an acute illness characterised principally by fever, cough and respiratory failure, caused by the Coronavirus SARS-CoV-2. It was reported for the first time in Wuhan in China at the end of 2019, and is now causing a pandemic. As of 12th April 2020 there were 78 995 confirmed cases in the UK, and 9875 deaths since the beginning of 2020. Globally the number of confirmed cases stood at 1, 696 588 with 105 952 deaths

### Current treatment for COVID-19 and IMP

Currently two medications have shown promise for treating severe COVID19: Dexamethasone {The, 2020, Dexamethasone in Hospitalized Patients with Covid-19 — Preliminary Report} and Remdesivir {Beigel, 2020, Remdesivir for the Treatment of Covid-19 - Preliminary Report. Reply}. No medication has yet been proved effective when started early when the disease is still milder. Several IMPs are currently in or about to start testing in clinical trials. An efficient approach to finding effective treatments against COVID-19 is to test existing antiviral agents that have previously been shown to be effective against other viral infections, including other members of the coronaviridae family.

The GETAFIX trial is testing the use of favipiravir as treatment for COVID-19. Favipiravir (T-705) is a pyrazinecarboxamide derivative. It is a pro drug which is converted to nucleoside analogue within the cell of interest, followed a series of phosphorylations to produce the active ribofuranosyltriphosphate T-705RTP which selectively inhibits viral RNA-dependent RNA polymerase.

### Non clinical studies with potential clinical significance

Favipiravir has shown potent *in vitro* inhibitory activity against seasonal influenza A (H1N1[2009], H2N2, H3N2, H5N1), avian influenza A (H7N9), influenza B, influenza C viruses, as well as against oseltamivir-resistant and amantadine-resistant strains.

It has also been shown to protect mice against Ebola virus Challenge (Oestereich *et al.* 2014) and has activity against RNA viruses including, Influenza, EBOV, arenaviruses and filoviruses. *In vitro* studies have demonstrated activity against Ebola and other RNA viruses (for example, Lassa

fever [*Arenaviridae*], *Bunyaviridae*, Chikungunya virus [*Alphavirus*]) via a similar mechanism of action .

Favipiravir effectively inhibits SARS-CoV-2 infection in Vero E6 cells (ATCC-1586) [7], The EC50 for COVID-19 *in vitro* is 61.88 µM, indicating an inhibitory effect (similar to that for Ebola virus) .

### **Previous use of Favipiravir in human patients**

Favipiravir has been used in more than 40 clinical studies, mainly in the US and Japan (33 Phase I, 3 Phase II and 4 Phase III). It has a favourable safety profile with a low frequency of mild to moderate adverse events (AEs), notably mild to moderate, asymptomatic elevations in serum uric acid and mild to moderate diarrhoea. It has also been used to treat acute Ebola Virus Disease in Guinea in a clinical trial which was not significant but had promising trends (JIKI trial) , and has been used in a trial to treat Ebola Virus in Sierra Leone. Previous use of favipiravir to treat patients with COVID-19 specifically is discussed below.

#### **1.1 IMP: Prior Experience in COVID-19 and dose selection**

There are limited, recent reports of the use of favipiravir for treatment of COVID-19 in the context of clinical trials performed in China. Cai *et al.*  reported the results of an open label Control study comparing favipiravir (35 patients) vs Lopinavir/Ritonavir (R) (45 patients) for the treatment of COVID-19. Both arms also received interferon-alpha by aerosol inhalation. Favipiravir shortened the viral clearance time from 11 days to 4, and showed significant improvement in chest imaging (91% vs. 62%). Patients taking favipiravir also had fewer adverse events than those taking Lopinavir/R. Chang Chen *et al.* 2020^12 have reported results from a prospective, multicentre, open-label randomised superiority trial comparing: favipiravir (N=116) to Arbidol (N=120). Clinical recovery within 7 days was 55.9% in the Arbidol group and 71.4% in the favipiravir group. This study concluded that favipiravir was the preferred treatment for non-severe COVID-19.

To date, six Chinese studies (other than the trial that has already reported results by Cai *et al.*) exploring the use of favipiravir against COVID-19 have been posted to the Chinese Clinical Trial Registry website. 

A randomised (1:1) trial has been posted by researchers in Egypt to the clinicaltrials.gov website. This trial will randomise patients to receive favipiravir (1600mg BD day 1 and 600mg BD days 2-10)

or standard of care therapy, which the investigators define as oseltamivir 75mg BD for 5-10 days and hydroxychloroquine 400mg BD day 1 followed by 200mg once daily from day 2 to day 5-10. This trial has reported that it has completed recruitment but has not yet reported results.

### **Rationale for dose selection**

In a clinical pharmacology study in which 1800mg of favipiravir was administered twice daily on Day 1 and 800mg of favipiravir was administered twice daily on Day 2 and thereafter (1800/800mg twice daily) for 22 days to healthy Japanese adult males aged 20 to 39 years, the peak plasma concentration of favipiravir remained at approximately 87 to 104µg/mL on Day 5 and after, and  $C_{min}$  remained at approximately 56 to 75µg/mL after the 2nd administration on Day 1. This value exceeds 9.72µg/mL, the  $EC_{50}$  of favipiravir for the SARS-CoV-2 virus and is significant even when the human protein binding rate of favipiravir of approximately 50% is taken into consideration. The Jiki trial for Ebola, used a dose of 6000 mg on day 1, and 2400mg on days 2 to 10 and reported no grade 3 or 4 adverse events. The clinical trial that recruited from Sierra Leone used a dose of 1600mg twice daily on D1 and 600mg daily days 2-14. The  $EC_{50}$  for Ebola for favipiravir is slightly higher than for COVID-19 at 10.5µg/mL.

The licensed dose in Japan of favipiravir for severe influenza is 1600mg twice daily on day 1 followed by 600mg twice daily for 4 days and the Japanese Association for Infectious Diseases have recommended the dosage and administration of favipiravir for COVID-19 as 3600 mg (1800 mg twice daily Day 1) followed by 1600 mg (800 mg twice daily Day 2 and thereafter) administered for up to 14 days.

The dose of favipiravir used in the recently completed clinical trials for patients with COVID-19 was 1600mg twice daily on D1 and 600mg twice daily days 2-14. In the trial reported by Cai *et al.*, patients also received aerosolized interferon-alpha treatment (5 million units twice daily). The interquartile range of time for viral clearance was 2.5 to 9 days (median 4) in the favipiravir plus aerosolised interferon arm compared to 8-13 days (median 11) in the control arm taking lopinavir/ritonavir.

Considering the previous available evidence, the dose proposed for COVID-19 in the GETAFIX trial is 3600mg on day one followed by 1800mg on days 2 to 10. This should maintain the  $EC_{50}$  above the

required concentration of 61.88microM (9.72microg/ml) and allow investigation of the efficacy of the single agent regimen.

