### **Treatment**

Patients will be randomised on a 1:1 basis to the following arms:

Control Arm: Standard Treatment for COVID-19 infection

OR

Experimental Arm: Standard Treatment for COVID-19 plus favipiravir:

- Day 1: Loading Dose favipiravir 1800mg (9 x 200mg tablets) 12 hours apart (2 doses)
- Days 2 -10 Maintenance Dose favipiravir 800mg (4 x 200mg tablets) every 12 hours (18 doses).

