### 5.1 Treatment Arms

Patients who are eligible for this trial will be registered/randomised to receive either:

Control Arm: Standard Treatment for COVID-19 infection

OR

Experimental Arm: Standard Treatment for COVID-19 plus favipiravir:

- Day 1: Loading Dose favipiravir 1800mg (9 x 200mg tablets) 12 hours apart (2 doses)
- Days 2 -10: Maintenance Dose favipiravir 800mg (4 x 200mg tablets) every 12hours (18 doses).

Subjects entering the study with a Child-Pugh liver impairment of grade A should receive the same loading dose but a reduced maintenance dose of favipiravir 600 mg twice daily on Days 2 through 10.

***It is strongly advised that the first dose of favipiravir is administered within 24 hours of the treating clinician receiving a positive valid SARS-CoV-2 test result.***

Treatment to continue until complete, unless there are unacceptable toxicities or other appropriate reasons for stopping treatment before completion.

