#### **6.2.2 Medication Errors and Overdose**

Medication errors, while not considered an AE or a SAE, may require monitoring and follow-up. Medication errors that result in SAEs should be reported as SAEs.

An overdose is defined as any dose greater than the highest daily dose included in this document. Any overdose must be recorded. If the overdose is associated with an AE, that AE must be recorded, assessed for seriousness, and reported as an SAE.

Any medication overdoses should be reported to the CRUK CTU Project Manager and Sponsor Pharmacist.

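### The dose rationale and the treatment section give different maintenance doses; separately, the overdose definition applies one loading-day ceiling to every study day and patient group

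*Protocol*

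**What the plan says.** **Maintenance dose.** The dose rationale in section 1.1 concludes that the dose for GETAFIX "is 3600mg on day one followed by 1800mg on days 2 to 10". For the same days the Trial Summary (Treatment) has "Maintenance Dose favipiravir 800mg (4 x 200mg tablets) every 12 hours (18 doses", and section 5.1 agrees with the summary: "Maintenance Dose favipiravir 800mg (4 x 200mg tablets) every 12hours (18 doses". Day 1 is not in dispute. Section 5.1 gives "Loading Dose favipiravir 1800mg (9 x 200mg tablets) 12 hours apart (2 doses", a total of 3600 mg, and the summary and section 1.1 give the same total. For patients who enter with Child-Pugh grade A impairment, section 5.1 prescribes a "reduced maintenance dose of favipiravir 600 mg twice daily on Days 2 through 10".

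**Overdose.** Section 6.2.2 states: "An overdose is defined as any dose greater than the highest daily dose included in this document". Every overdose is to be recorded and notified to the project manager and the sponsor pharmacist. In addition, "If the overdose is associated with an AE, that AE must be recorded, assessed for seriousness, and reported as an SAE". The definition mentions neither study day nor treatment phase nor hepatic group, and it does not refer to section 5.1. Section 1.1 also cites, as background, an Ebola trial that "used a dose of 6000 mg on day 1, and 2400mg on days 2 to 10".

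**The concern.** Two things look wrong, and each stands without the other.

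First, the section that justifies the dose describes a maintenance regimen different from the one the treatment section prescribes. The exposure argument in section 1.1 is therefore attached to a regimen that section 5.1 does not give.

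Second, the overdose rule takes its ceiling from the largest daily dose anywhere in the document. Day 1 is the heaviest day, so the loading total becomes the yardstick for the nine maintenance days and for patients on the reduced dose. An error of ordinary kind, such as repeating the loading dose on day 2, would not meet the definition. What is at stake is classification. Section 6.2.2 attaches three duties to an overdose: recording it as such, reporting an associated adverse event as an SAE, and telling the project manager and sponsor pharmacist. Section 7.1.5 tabulates all SAEs, so the SAE rule also affects which events reach that table.

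**Working it through.** **Inputs.** 200 mg tablets; 9 tablets twice on day 1; 4 tablets twice daily on days 2 to 10, 18 doses (Trial Summary; 5.1). 600 mg twice daily on days 2 to 10 for Child-Pugh A (5.1). 1800 mg on days 2 to 10 (1.1). 6000 mg on day 1 of the cited Ebola trial (1.1).

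**Step 1: daily totals.**
- Day 1: 9 × 200 × 2 = 3600 mg. This reproduces the figure in section 1.1, so that sentence is written in daily totals.
- Days 2 to 10, summary and 5.1: 4 × 200 × 2 = 1600 mg a day.
- Days 2 to 10, section 1.1: 1800 mg a day.
- Child-Pugh A: 600 × 2 = 1200 mg a day.

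**Step 2: size of the conflict.** 1800 − 1600 = 200 mg a day; 200 / 1600 = 12.5%. Over nine days: 9 × 1800 = 16.2 g against 9 × 1600 = 14.4 g. Whole course: 3.6 + 16.2 = 19.8 g (99 tablets) against 3.6 + 14.4 = 18.0 g (90 tablets). If the 1800 mg were read as a single dose rather than a daily total, the gap from 5.1 would be wider.

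**Step 3: does the conflict move the overdose ceiling?** Ceiling = the largest daily dose in the trial regimen. With 1600 mg maintenance: max(3600, 1600, 1200) = 3600 mg. With 1800 mg: max(3600, 1800, 1200) = 3600 mg. It does not move.

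**Step 4: what the ceiling lets through on days 2 to 10.** Ratio = ceiling / stated daily dose.

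| Stated daily dose | Ceiling 3600 mg (trial's own maximum) | Ceiling 6000 mg (every printed dose counted) |
|---|---|---|
| 1600 mg (summary, 5.1) | 2.25 | 3.75 |
| 1800 mg (1.1) | 2.00 | 3.33 |
| 1200 mg (5.1, Child-Pugh A) | 3.00 | 5.00 |

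**Step 5: two cases under the 3600 mg reading.**
- A patient repeats the loading day during maintenance: 18 × 200 = 3600 mg, which is not greater than 3600 mg. If the supply is the 90 tablets implied by 5.1, it would last 90 / 18 = 5 days at that rate, and no day would meet the definition.
- A Child-Pugh A patient takes 1600 mg a day in place of 1200 mg: 1600 / 1200 = 1.33 times the stated dose, and well under the ceiling.

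**The case against.** The other side has several good points.

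- **The two defects are not cause and effect.** A reader might infer that the conflicting maintenance doses leave the overdose threshold undetermined. They do not: step 3 gives 3600 mg whichever figure stands.
- **The 6000 mg ceiling is strained.** That dose belongs to another trial and is cited as background. In a safety section of this protocol the natural reading is this trial's own maximum. The loose wording permits the larger figure, and that is a reason to tidy it, but the 3.75-fold and 5-fold ratios should not carry the argument.
- **Excess intake is not invisible.** A reader might infer that maintenance overdoses would go unrecorded. The protocol does not support that. All deviations are to be notified (10.3); home patients keep a dose diary and return remaining drug (5.5), with a compliance check at day 15 or the next visit (4.2.2); patient accountability logs are required (5.3.1); adverse events are documented in full (6.1.2); SAEs are reported whatever the dose (6.1.4), as are transaminases above three times the upper limit; and a medication error that results in an SAE is reported (6.2.2). An IMP Management Document, not available here, may add more.
- **Operative text agrees.** The summary and 5.1 match each other and give tablets, interval and number of doses. The 1800 mg figure appears once, in the rationale, and nothing shows that anyone would dispense from it.
- **One ceiling is not in itself a contradiction.** It is a choice that fits a regimen with a loading day poorly.

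What remains is narrower but real. The other routes do not carry the overdose label or its notice duty. A non-serious adverse event after excess intake on a maintenance day generally has no path to SAE reporting except through the overdose rule. The diary and returned drug come back only at day 15 or later, and the daily calls to outpatients on days 1 to 10 are specified for adverse events, concomitant medication and the WHO scale, not for tablet counts.

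**Conclusion.** Both defects stand, separately.

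1. The maintenance dose is stated inconsistently: 1800 mg a day in section 1.1 against 1600 mg a day in the summary and section 5.1, a difference of 12.5%. This is certain from the text.
2. The overdose definition, read naturally, sets 3600 mg as the ceiling on every day. Intake on days 2 to 10 up to 2.25 times the 1600 mg in 5.1, or 3 times the Child-Pugh A dose, falls outside it. The loss is one of classification and reporting route, not of all recording.

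The second conclusion assumes that the rule compares a day's total intake with the ceiling, and that only this trial's doses count. How often such intake would occur cannot be sized: the protocol gives neither the share of patients treated at home nor an expected rate of dosing errors. A claim that the safety record as a whole would be incomplete therefore goes further than the documents allow. The efficacy analysis and sample size are untouched. Correction is advisable before further use of the document.

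**What to change.** Reconcile the days 2 to 10 figure in section 1.1 with the Trial Summary and section 5.1, so that one maintenance dose stands throughout.

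Reconcile section 6.2.2 with the regimen in section 5.1, so that the overdose reference is determinate for each study day and patient group and cannot draw on doses cited from other trials. A bare cross-reference to 5.1 is not enough: while the words *highest daily dose* remain, the ceiling stays at 3600 mg on every day. Which dose and which threshold are correct is for the sponsor's clinical team and pharmacist; no view is taken here. The IMP Management Document should be checked for the same two points.

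The cost is a text amendment and a note to sites and pharmacies. No trial procedure, sample size or analysis changes as a result of the rewording itself.
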